### Data management and storage

Data from the participants will be directly entered via tablets into a specifically designed database (REDCap). Data collected using the paper–pencil procedure will be afterward entered in the database (REDCap) by a data manager. Incoming data will be continuously monitored and checked for plausibility, quality, and completeness by a data manager. All data will be stored in pseudonymized form in the database. Only authorized and trained study personnel will receive a login-roll in line with their task (e.g., research assistant to start screening, data manager for query management, data entry, data validation, and plausibility checks). For the purpose of long-term storage, the original, pseudonymized data (after database lock) will be stored at Ulm University.

An anonymized participant-level data will be made available on request to scientific colleagues after publication of the results.

### Statistical analysis

The primary outcome (CATS-2 self-report) will be analyzed using mixed effects models (MEM) with fixed effects of group (CBITS vs. TAU +) and time (baseline T0 versus 4-month follow-up T1) as well as their interaction (*α* = 0.05). Based on the longitudinal design of the data structure, data will be nested by participants; and repeated measures will be modeled using an unstructured covariance matrix. Since MEMs can handle missing data within the longitudinal data structure, the analyses will be performed with the ITT sample including all randomized participants (*N* = 90). We will use exploratory MEMs for the secondary outcomes. Additionally, per-protocol analyses will be performed for all outcomes.

We could identify several factors that might be related to dropout in children who receive trauma-focused treatment such as number of traumatic events (e.g., [35]). Hence, we will run a sensitivity analysis with the following variables: child age and gender, pre-treatment PTSS level, number of traumatic events, and type of treatment. In more detail, we will run the analysis while controlling for these potential covariates, repeat the analysis not controlling for the factors, and check for differences in the results. When finding the differences, we will use the model with the covariates to allow for making the assumption of missing at random for an unbiased effect estimate. Accounting for non-compliance is not necessary for the ITT analyses. For the per-protocol analyses, we will adjust for possible covariates for non-compliance in order to assume strong ignorability plausible. Effect sizes will be calculated by Cohen’s *d* [36]. A significance level of *α* = 0.05 will be used. Exploratory subgroup analyses for known PTSS outcome predictors (e.g., age, sex, baseline PTSS) will be performed. Safety: We will compare the frequency of SAEs between conditions using the *χ*^2^ tests (*α* = 0.05). No interim analyses will be performed on the main outcomes.

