### Sample size

Based on the literature and our planned analyses on the effectiveness of CBITS for children, we expect a moderate effect size of *d* = 0.7 for the CBITS intervention. An attempt was made to estimate the likely effect size based on longitudinal studies reporting on children and adolescents living in the child welfare system: In our own trial of unaccompanied refugee minors, we found an effect size of *d* = 0.15 for routine care in child welfare programs [18]. A Swiss study investigating externalizing behavior problems in institutionalized adolescents over the course of 1 year found effects of *d*_girls_ = 0.28 and *d*_boys_ = 0.24 [19]. Another study investigating emotional and behavioral symptom trajectories of children in long-term out-of-home care in an English local authority found that the largest trajectories were chronic symptom profiles, in which young people were rated in the abnormal range from their first year in care and remained in this range (based on the descriptive statistics reported we calculated *d* = 0.02–0.1 for emotional problems [20]). Based on these studies, we assume a mean effect size of *d* = 0.1 for routine care for children in child welfare programs. As children and adolescents randomized to TAU + will also receive a report with a treatment indication, we assume that a small proportion in TAU + condition (10–20%) will find their way to local service providers. For those receiving psychotherapeutic treatment from local service providers, we assume a mean effect size of *d* = 1.0 based on therapy as usual conditions in other trials (e.g., [21]). In sum, based on the before-mentioned literature on routine care in child welfare systems and the assumption that a small proportion will receive treatment at local service providers, we assume an overall mean effect size of *d* = 0.3 for the TAU + condition. Following the expected effect size of *d* = 0.7 for CBITS and *d* = 0.3 for TAU + , we assume a controlled effect size of *d* = 0.4 between conditions at 4-month follow-up (T1) in favor of CBITS on the primary measure of PTSS (CATS-2). A power analysis conducted with G*Power for the within-(time)-between-(condition)-interaction requiring a power of 0.80 and *α* = 0.05 (two-tailed), a correlation of *r* = 0.3 among replicated measures (based on our previous own RCTs [18, 22]) estimates a sample size of *N* = 72 (*n* = 36 per condition) to detect the controlled effect size of *d* = 0.4 for the primary outcome between conditions. With an assumed dropout rate of about 20% across both conditions, an oversampling of *n* = 18 participants is needed, resulting in an overall sample of *N* = 90 participants (*n* = 45 per condition; *n* = 22–23 per participating site).

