### Methods against bias

Random allocation of participants is ensured by the trial design. Stratification by CATS-2 will ensure comparability for PTSS at baseline (T0). The CBITS training will be highly standardized and implemented by certified intervention trainers, treatment fidelity will be ensured by ongoing case consultations and by session checklists. Compensation of the additional training time as part of the regular training and providing access to an otherwise expensive additional clinical training without extra costs will reduce the selectivity of the therapist population under study. The blinding of the participants and therapists is not possible. Study assessors will not be blinded by condition either, but only self-report measures will be used and not clinician-rated interviews. All outcomes on the participant, caregiver, and therapist levels are psychometrically sound and well-established measures. Primary and secondary outcomes are determined in the study protocol to avoid selective reporting (reporting bias/publication bias). Data records will be kept as up-to-date as possible by means of online symptom monitoring and documentation of treatment sessions. All available follow-up data will be included in the final analyses, thus investigating an intention to treat (ITT) population of participants. The mixed model analysis will take missing data and different numbers of reassessments per participant into account. The trial is preregistered at https://clinicaltrials.gov/, and its results will be published irrespectively of significant results to avoid publication bias. The publication of results will be in line with the CONSORT guidelines.

Important protocol modifications will be communicated to trial registries, journals, regulators, funders, advisory board, and DSMB right away via e-mail and conference calls. Trial participants will be informed by letters.

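### The primary group-by-time test leaves the baseline group difference free, so it is less precise than a baseline-constrained model: about 43% more variance at r = 0.3, 20% dropout and equal SDs, less if the T0 SD is narrower

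*Protocol article*

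**What the plan says.** The Statistical analysis section of the Protocol article sets a mixed model for self-reported CATS-2 with fixed effects of group and "time (baseline T0 versus 4-month follow-up T1) as well as their interaction", and adds that "repeated measures will be modeled using an unstructured covariance matrix". Everyone randomised is to be included. T0 is therefore a response, and the group main effect gives each arm its own T0 mean.

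The Sample size section describes the same test: "A power analysis conducted with G*Power for the within-(time)-between-(condition)-interaction", "requiring a power of 0.80", alpha "0.05 (two-tailed", and a correlation of 0.3 "among replicated measures (based on our previous own RCTs [18, 22". It assumes a difference of d = 0.4 between arms at T1, needs 72 children, and recruits 90 to allow for about 20% dropout.

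Under Trial design, children are randomised only after the T0 screening of their facility is complete, in blocks stratified by CATS-2. Methods against bias states the purpose: "Stratification by CATS-2 will ensure comparability for PTSS at baseline (T0".

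Baseline PTSS also appears as one of several covariates in a sensitivity analysis motivated by dropout. That covariate model is preferred only if its results differ from those of the unadjusted model.

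**The concern.** Because T0 comes before randomisation, the true baseline difference between arms is zero by design. The planned model spends information estimating it, and the noise in that estimate passes into the interaction. When the T0–T1 correlation is as low as 0.3, subtracting the whole baseline value adds more noise than it removes. A contrast that uses T0 only as far as it predicts T1 targets the same T1 effect with a smaller standard error.

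At stake is the width of the confidence interval for H1 in a small trial. The loss can be avoided with the data already planned.

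**Working it through.** **The plan's own figure.** G*Power's within-between interaction uses λ = N·m·f²/(1−r). With N = 72, m = 2 time points, f = 0.2 and r = 0.3, λ = 72 × 2 × 0.04 / 0.7 = 8.23, and the power is 0.808. At N = 70 it is 0.796. So N = 72 reproduces, and 72 / (1 − 0.20) = 90. The interaction is therefore the test that was sized.

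**Inputs.** r = 0.3, 45 children per arm, a share m = 0.20 missing T1, and a T1 difference of 0.4 SD (all from Sample size). Assumption: T1 SD = 1 and T0 SD = k. The documents give neither SD, so k is varied.

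**Complete data, k = 1.** Variances below are per child, in units of the T1 variance.
- Planned interaction (difference in mean change): 2(1−r) = 1.40
- Baseline-adjusted contrast: 1−r² = 0.91
- Ratio: 1.40 / 0.91 = 1.538, an excess of 54%

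**With T1 missing and all randomised children kept** (missingness equal in both arms), the variance of the group contrast with n per arm is:
- T0 means free: 2·[(1−r²)/(n(1−m)) + (k−r)²/n]
- T0 means constrained equal: 2·(1−r²)/(n(1−m))
- Ratio: 1 + (k−r)²(1−m)/(1−r²)

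At r = 0.3 and m = 0.20:

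| T0 SD / T1 SD (k) | Excess variance | Wider CI |
|---|---|---|
| 1.0 | 0.49 × 0.8 / 0.91 = 43% | 20% |
| 0.9 | 0.36 × 0.8 / 0.91 = 32% | 15% |
| 0.8 | 0.25 × 0.8 / 0.91 = 22% | 10% |
| 0.7 | 0.16 × 0.8 / 0.91 = 14% | 7% |

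The last column is the square root of the variance ratio, minus 1. A separate generalised-least-squares calculation with unstructured covariance, 45 per arm and k = 1 gives ratios of 1.538 (complete data) and 1.431 (20% missing).

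**Other correlations.** With k = 1 and complete data the excess is (1−r)/(1+r): 33% at r = 0.5 and 18% at r = 0.7. With 20% missing these become 27% and 14%.

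**Power with 90 randomised, 20% missing T1, k = 1 and a true T1 difference of 0.4 SD** (normal approximation):
- Planned: variance 2 × (0.91/36 + 0.49/45) = 0.0723, SE 0.269, 0.4/0.269 = 1.487, power Φ(1.487 − 1.960) ≈ 32%
- Constrained: variance 2 × 0.91/36 = 0.0506, SE 0.225, 0.4/0.225 = 1.779, power Φ(1.779 − 1.960) ≈ 43%

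**The case against.** **The planned test is valid, and it is the one the sample size was built on.** This stands. In simulation with 36 per arm both estimators were unbiased. A reader might infer a biased or invalid analysis, but the documents do not support that. The point is one of efficiency.

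**The 54% could be read as the loss in this trial.** It requires complete data and equal SDs. The plan expects about 20% dropout and keeps children who have T0 only. The 21-point entry threshold may also narrow the T0 SD. A related inference, that ignoring baseline altogether would beat the planned test, also depends on the SDs: with complete data it reverses once k falls below 2r = 0.6.

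**The low absolute power could be blamed on the model.** It should not be. N = 72 reproduces only with f = 0.2, which in this 2×2 interaction is a difference in change of 0.8 raw SD. That is a separate sample-size matter. Only the gap of about 11 points belongs here.

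**The truncated T0 could be called unsuitable as a normal response.** The constrained model also treats T0 as a response, so this is no reason to prefer it. With complete data the difference in mean change needs no normality to be estimated.

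**Baseline is already covered, by stratification and by the sensitivity analysis.** It is true that T0 CATS-2 is not ignored. Close balance, however, does not shrink the standard error that the planned model reports. In a simulation with 36 per arm, complete data and pairwise-balanced baselines, the planned test became conservative (type I error about 1.5%), with power of 0.25 against 0.42 for baseline adjustment. The protocol does not say how fine its strata are, so this is an extreme case. The sensitivity analysis is adopted only if results differ. Moreover, a baseline main effect added to a model that already has T0 as a response does not turn the interaction into a baseline-adjusted contrast.

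**Conclusion.** The concern holds as a loss of precision. The primary contrast leaves free a baseline difference that the design makes zero in expectation. At r = 0.3 with 20% of T1 missing, its variance is about 43% too large if the T0 and T1 SDs are equal, and about 14% to 32% too large if the T0 SD is 0.7 to 0.9 of the T1 SD. The excess is smaller at higher correlations. With 90 randomised, equal SDs and a true difference of 0.4 SD, this means power of about 32% rather than 43%.

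These sizes rest on the plan's own r and dropout rate, missingness equal in both arms, and an SD ratio that the documents do not give. The direction does not depend on the ratio: (k−r)² is never negative, so in large samples the constrained model is never less precise. The change is worth making, but the planned analysis is not invalid without it.

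**What to change.** Before outcomes are analysed, make the primary analysis the same mixed model with the T0 means of the two arms constrained equal. Drop the group main effect, keep time (T0 as reference level) and group-by-time, and keep the unstructured covariance. The group-by-time term is then the baseline-adjusted difference at T1. All randomised children stay in, so the intention-to-treat set is unchanged.

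A model for T1 CATS-2 with continuous T0 CATS-2 as covariate can be a supporting analysis. It is not interchangeable with the constrained model here, because it drops children without T1. Use the constrained form for secondary outcomes that have a T0 value.

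The cost is a documented amendment to protocol and registry, circulated as Methods against bias requires for important modifications, and a matching line in the Sample size section. No new data are needed.

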The total duration for one participant in the trial from screening to the 10-month follow-up is estimated for about 12 months. The individual participant and the respective caregiver will participate in three study visits at the respective child welfare facility (baseline assessment (T0), post-treatment/4-month follow-up assessment (T1), and 10-month follow-up assessment (T2)). All participants will complete self-report questionnaires via the platform REDCap and caregivers (child welfare staff) will complete respective proxy reports via paper–pencil or REDCap, at each assessment time point. At the end of every assessment, the participant will receive a brief feedback on the PTSS, depression, and anxiety scores by the researchers, and a brief written report will be sent to each participant via mail several days after each assessment. The inclusion and exclusion criteria will be assessed at T0. After the inclusion of all participants in the child welfare program, the participants will be randomized to either CBITS or TAU + by sending a list to the randomization center. The outcome of the randomization will be communicated via phone to the child welfare project coordinator and also sent via mail in an official letter. The time span between randomization and the first treatment session should be no longer than 4 weeks. After randomization, the study staff will match a trained therapist to the intervention group and help organize the intervention sessions both with the therapist and the child welfare project coordinator (who will inform participants and caregivers). In each intervention session, the therapist will assess all participants with the CATS-2 ICD-11 PTSD short version via paper–pencil format, collect the questionnaires, and submit them to the study staff. The therapists and participants will complete an alliance rating after the first session and after the last session of the CBITS intervention and the therapists complete a fidelity rating after each CBITS session. The fidelity ratings and CATS-2 symptom monitoring data will be added to an online survey (www. unipark.de) by the therapist after each session.

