### CBITS

The CBITS program is a skills-based trauma group and individual intervention, which uses evidence-based cognitive-behavioral techniques (e.g., psychoeducation, relaxation, social problem solving, cognitive restructuring, and exposure) and is designed to be delivered by mental health professionals. The theoretical underpinnings are based on cognitive behavioral theory regarding anxiety and trauma. The program consists of ten 45-min group sessions (about six to eight students/participants per group), one to three individual sessions, two child welfare staff psychoeducational sessions, and one parent/caregiver session. For this study, we will specifically train and supervise study therapists to deliver the intervention within child welfare programs. For children in child welfare, CBITS offers several advantages over traditional community-based, individual-level treatment models. First, with its focus on trauma, CBITS has been shown to influence PTSS, depression, anxiety, and school behavior, making it an ideal means to target the diverse problems that children in child welfare face. Second, unlike traditional community mental health services, CBITS is most often provided outside of the clinical setting, making it possible to keep youth in place to receive the program rather than pulling them away for clinic-based treatment. Third, the group format of CBITS broadens the reach of the intervention, making it possible to serve more youth than a traditional individual-based therapy model. From an ethical standpoint, it seems highly appropriate to provide this vulnerable population with a helpful trauma-focused group intervention.

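### The primary model has participant as its only level, so correlation within CBITS therapy groups, which arises in one arm only, is left out of both the test of H1 and the sample size.

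*Protocol article*

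**What the plan says.** Under Statistical analysis, the protocol article gives the primary model fixed effects of condition, time (T0, T1) and their interaction, and adds that "data will be nested by participants; and repeated measures will be modeled using an unstructured covariance matrix". No term for therapy group, therapist or institution is named. The sensitivity-analysis covariates (age, gender, baseline PTSS, number of traumatic events, type of treatment) do not supply one.

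The CBITS section describes "ten 45-min group sessions (about six to eight students/participants per group", plus individual and caregiver sessions. Under Procedure (Participants), once randomisation is done "the study staff will match a trained therapist to the intervention group". Under Trial design, randomisation is of individuals within each child welfare programme, half to each arm. TAU+ involves no therapy group before T1.

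The Sample size section assumes a between-condition effect of *d* = 0.4 and "a correlation of *r* = 0.3 among replicated measures", and arrives at 72 evaluable and 90 randomised participants. It mentions neither an ICC nor a design effect.

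**The concern.** Children in one CBITS group share a therapist, the other group members and the course of the sessions. Their T1 scores may therefore be more alike than those of children in different groups. TAU+ has no counterpart to this, so the design is partially nested. The unstructured covariance matrix describes the T0–T1 correlation within one child; it cannot carry correlation between children. Randomising individuals within institutions does not remove the dependence, because treatment creates it after randomisation.

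H1 is the hypothesis of the primary objective, and its p-value and confidence interval come from this model. If the group-level variance is positive and nothing offsets it, the standard error is too small. The secondary outcomes would be affected in the same way, but the protocol labels those tests exploratory, so less depends on them.

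**Working it through.** **The plan's own figure.** Inputs from Sample size: *d* = 0.4, so *f* = 0.2; two time points; *r* = 0.3; two-sided α = 0.05; power 0.80. For the within-between interaction in G*Power, λ = f²·N·2/(1 − r). At N = 72, λ = 0.04 × 72 × 2/0.7 = 8.23. With 1 and 70 degrees of freedom the power is 0.808; N = 70 gives 0.796. Allowing 20% dropout, 72/0.8 = 90. Both stated figures reproduce, under independent participants.

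**Number of groups.** With 45 children in CBITS, 45/8 = 5.6 and 45/6 = 7.5, so about 6 to 8 groups.

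**Formula.** With complete data, the group-by-time test of the stated model is the two-sample test on change scores. For group size m and share ρ of the change-score variance that lies between groups in the CBITS arm:
- design effect in CBITS: DE = 1 + (m − 1)ρ
- variance ratio of the contrast: R = (1 + DE)/2
- actual type I error: 2[1 − Φ(1.96/√R)]

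**Which ICC.** Groups form after baseline, so the group effect sits at T1. With equal unit variances at T0 and T1 (assumed) and *r* = 0.3, the change score has variance 1 + 1 − 2 × 0.3 = 1.4. A T1 ICC therefore becomes ρ = ICC/1.4: 0.02, 0.05 and 0.10 become 0.0143, 0.0357 and 0.0714. If the assumed ICC refers directly to the change score, ρ = ICC.

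Example, m = 6 and T1 ICC 0.05: DE = 1 + 5 × 0.0357 = 1.179; R = 1.089; type I error 6.0%.

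| Assumed ICC | On T1 score, m = 6 / 8 | On change score, m = 6 / 8 |
|---|---|---|
| 0 | 5.0% / 5.0% | 5.0% / 5.0% |
| 0.02 | 5.4% / 5.6% | 5.6% / 5.8% |
| 0.05 | 6.0% / 6.5% | 6.5% / 7.1% |
| 0.10 | 7.1% / 8.0% | 8.0% / 9.2% |

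Simulation agrees. Six groups of six gave 6.1% and 7.2% at T1 ICC 0.05 and 0.10. On the change-score reading, 40,000 runs per setting gave 6.3–6.9% and 8.0–9.3%.

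**Smaller groups.** If the ten programmes listed under Trial status shared the sample equally (an assumption), 45/10 = 4.5 CBITS children per programme. Then R = 1 + 3.5ρ/2. For T1 ICC 0.05 and 0.10, R = 1.0625 and 1.125, giving 5.7% and 6.5%. On the change-score reading the figures are 6.0% and 7.1%.

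**Omitted institution level.** Suppose institutions also differ in change over time, equally in both arms, with a change-score ICC of 0.10. Because each institution contributes to both arms, omitting this level makes the test conservative. Simulated type I error for groups of 6 to 8 is 4.0–4.2% with no group effect. At change-score group ICCs of 0.02, 0.05 and 0.10 it is 4.6–5.0%, 5.5–6.1% and 7.0–8.5%. For six groups of six at T1 ICC 0.05 and 0.10 it is about 5.5% and 6.6%.

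**Power with the group level modelled.** Replace N = 72 by 72/R in the protocol's own calculation. On the change-score reading, ICC 0.05 gives R = 1.125 to 1.175, an effective N of 64.0 to 61.3 and power 0.76 to 0.74. ICC 0.10 gives R = 1.25 to 1.35, an effective N of 57.6 to 53.3 and power 0.71 to 0.68. These figures come before any loss of degrees of freedom from having few groups.

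**The case against.** The strongest points on the other side are these.

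- **No ICC is given.** A reader might infer from the design alone that the type I error exceeds 5%. The document does not support that: the excess requires a positive within-group correlation, and at ICC 0 the test holds at 5.0%. Under the strict null, where CBITS changes no child's outcome, no treatment-created clustering exists. Inflation arises when the mean effect is zero but effects vary between groups. This stands, and the claim must be conditional. It does not remove the defect, since H1 concerns the average effect and its interval should allow for variation between groups.
- **The institution omission works the other way.** This also stands. At a change-score group ICC of 0.02 and institution ICC of 0.10 the offset is complete; at 0.05 and 0.10 it is partial. Two omissions that may cancel are not error control.
- **Groups may be small, and one group per programme is inferred.** With 20% dropout, groups of 6 to 8 leave about 4.8 to 6.4 evaluable children, which lowers the figures. A large programme might form two groups. Neither changes the structure.
- **The article is condensed and a separate analysis plan may exist.** The nesting sentence is tied to the longitudinal structure and does not expressly exclude further random effects. That limits the severity. Still, the article states participant nesting positively, and its sample size makes no allowance for groups.

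A reader might also infer that the planned test loses power to the extent shown above. It does not: those figures belong to a test that models the groups. On the protocol's G*Power basis, the simulated rejection rate of the participant-only test (six groups of six) moves only from 0.808 to 0.796 and 0.784 at change-score ICC 0.05 and 0.10.

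**Conclusion.** The point holds conditionally. As written, the primary model and the sample size ignore a source of correlation that the design creates in the CBITS arm only. If T1 outcomes correlate within CBITS groups, the test of H1 can be anti-conservative by roughly half a percentage point to three points over T1 ICCs of 0.02 to 0.10 and groups of 6 to 8. The excess shrinks with smaller evaluable groups, and can shrink or vanish if institutions differ in change over time.

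These sizes rest on assumed ICCs, equal variances at T0 and T1, *r* = 0.3 and complete data. A certain breach of the 5% level is not shown. The stated 80% power likewise holds only under independence. This is a should-fix.

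**What to change.** Before outcomes are analysed, amend the primary model to include:

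1. an institution term, including institution by time, because randomisation is within institution;
2. a random therapy-group effect at T1 that applies to the CBITS arm only (a partially nested model);
3. Kenward-Roger or Satterthwaite degrees of freedom.

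The institution term is needed alongside the group effect. Without it, where there is one group per programme, the group effect would absorb institution variance that cancels from the within-institution contrast, and the interval could be too wide.

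Report the estimated ICC. Restate the power for N = 72 under assumed ICCs: on the protocol's own basis about 0.74–0.76 at a change-score ICC of 0.05 and 0.68–0.71 at 0.10, before any small-cluster penalty.

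The cost is analysis wording. Study staff match therapists to groups, so the identifiers should exist. The downside is a slightly wider confidence interval and fewer degrees of freedom, with only about 6 to 8 groups to estimate the group variance.

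### The covariate rule ties the reported H1 model to an undefined comparison of results, and the adjusted model as written uses baseline PTSS both as outcome and as covariate

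*Protocol article*

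**What the plan says.** The Statistical analysis section of the protocol article sets the primary model for CATS-2 self-report as a mixed model with group, "time (baseline T0 versus 4-month follow-up T1) as well as their interaction". It adds that "repeated measures will be modeled using an unstructured covariance matrix". T0 CATS-2 is therefore one of the two responses for each child.

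The next paragraph introduces factors thought to be related to dropout and announces a sensitivity analysis with "child age and gender, pre-treatment PTSS level, number of traumatic events, and type of treatment". The analysis is run with these covariates. The team will then "repeat the analysis not controlling for the factors, and check for differences in the results". The rule that follows is "When finding the differences, we will use the model with the covariates", and the reason given is "to allow for making the assumption of missing at random for an unbiased effect estimate".

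The section does not define a difference, does not define the treatment-type variable, and does not say whether the covariate model then becomes the H1 result.

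**The concern.** Three features of this text need separate treatment.

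- **Which result is primary.** An analysis labelled as sensitivity can become the reported one after both results are seen, on a criterion nobody has fixed. The Methods against bias section says outcomes are fixed in the protocol to avoid selective reporting. The model for H1 should be fixed just as firmly.
- **Baseline on both sides.** A child's T0 score is a response row and, on the plain reading, also a predictor of that same row.
- **Treatment type.** Group is already in the model, so this covariate either repeats it or brings in something that happens after randomisation.

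At stake are whether the fall-back model can be fitted, whether its standard error is right, and whether the estimate is still the intention-to-treat effect that the plan promises.

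**Working it through.** **Inputs.** From the Sample size section: r = 0.3 between repeated measures, N = 72 analysed, 20% dropout, and effects of 0.7 (CBITS), 0.1 (routine care) and 1.0 (outside therapy, reached by 10–20% of TAU+). The stated total reproduces: 72/0.8 = 90. The plan gives no figure for the covariate rule itself.

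**1. Likelihood of the covariate model.** With T0 entered at a common slope c, the T0 row has mean b0 + b1·group + c·T0. Setting c = 1 and b0 = b1 = 0 makes every T0 residual exactly zero. An unstructured covariance leaves the T0 residual variance free, so the log-likelihood term −(N/2)·log(variance) grows without limit. Profile log-likelihood in one simulated data set (36 per arm, r = 0.3):

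| slope c | log-likelihood |
|---|---|
| 0 | 22.1 |
| 0.3 | 47.8 |
| 0.9 | 187.9 |
| 0.99 | 353.7 |
| 0.999 | 519.4 |
| 1 − 1e-8 | 1348.4 |

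Each tenfold approach to 1 should add N·ln 10 = 72 × 2.303 = 165.8. The table gives 519.4 − 353.7 = 165.7. The REML likelihood at N = 90 behaves the same way: −53, 141 and 334 at T0 residual SDs of 1.0, 0.1 and 0.01.

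**2. Effect on the estimate.** Let D0 and D1 be the arm differences at T0 and T1. With complete data the contrast is (D1 − c·D0) − (D0 − c·D0) = D1 − D0, so c cancels.

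**3. Standard error under a workaround.** An analyst who cannot fit the unstructured model may turn to compound symmetry. Simulation: 3,000 trials, N = 90, r = 0.3, REML. Two assumptions are not in the document: trauma count correlates 0.25 with PTSS, and dropout depends on T0 PTSS and, within CBITS, on trauma count. Results for a true effect of 0 and 20% dropout (Monte Carlo error about 0.004 on each rejection rate):

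| model | mean estimate | mean SE | empirical SD | type I error |
|---|---|---|---|---|
| unadjusted, unstructured | −0.022 | 0.269 | 0.267 | 0.047 |
| age, gender, trauma count, unstructured | −0.002 | 0.268 | 0.266 | 0.044 |
| the same plus T0 PTSS, compound symmetry | −0.001 | 0.245 | 0.266 | 0.071 |
| ANCOVA of T1 on T0 | −0.001 | 0.227 | 0.226 | 0.051 |

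The third model's SE is 0.245/0.266 = 0.92 of what it should be. With a true effect of −0.4 its mean estimate is −0.401. Without dropout, its estimate and SE match those of the unadjusted model.

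**4. Precision forgone.** Relative variances are 2(1 − r) = 1.4 for the change contrast and 1 − r² = 0.91 for ANCOVA. The ratio is 0.91/1.4 = 0.65, a 35% reduction. The complete-data simulation agrees: (0.200/0.247)² = 0.66. Entering T0 as in step 1 gains none of this, because the contrast stays the change score.

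**5. The switch.** Suppose a difference means disagreement on significance. If the models agree, the verdict is the same either way. If they disagree, the covariate model's verdict is used. The rule therefore always returns the covariate model's verdict, with that model's type I error (0.044 without T0 as covariate, 0.071 with it). If a difference instead means an estimate shift above 0.05 or 0.1, the rates are 0.045 and 0.047 without T0, and 0.056 and 0.049 with it.

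**6. Treatment type.** If it means arm, the fixed-effects design for group, time, their interaction and this term has 5 columns and rank 4, so the term is redundant. If it means treatment received, the plan's own figures give a TAU+ effect of (1 − s)·0.1 + s·1.0 for uptake s:

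- s = 0.10: 0.19, contrast 0.7 − 0.19 = 0.51
- s = 0.20: 0.28, contrast 0.7 − 0.28 = 0.42

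Adjusting for treatment received with a time interaction compares CBITS with untreated TAU+ only: 0.7 − 0.1 = 0.60.

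**The case against.** The strongest reply is that little of this damages the estimate. A reader might infer that the adjusted model cannot give a valid effect, or that the rule invites choosing by p-value. The documents support neither. The slope cancels from the complete-data contrast, and the compound-symmetry fit stayed unbiased under dropout. The direction of the switch is fixed in advance, towards the covariate model, and its stated reason is missing data, not significance. The section calls the exercise a sensitivity analysis and never says outright that it replaces the primary result.

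The degeneracy also depends on a reading. Pre-treatment PTSS level could mean the CATS-2 severity stratum, or could enter for T1 only, and then the T0 residual is not forced to zero. How a covariate is coded is often left to the analysis plan. The 0.071 depends on a covariance structure that the plan does not propose and on assumed dropout mechanisms. Treatment type may simply mean arm, which is harmless. Even treatment received, as a main effect only, leaves the complete-data interaction unchanged.

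The aim behind the covariates is sound: in the simulation, adding age, gender and trauma count removed the unadjusted model's bias of −0.022. Adjusting for baseline PTSS, the stratification factor, is also sound in itself.

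All of that stands, and it limits the severity. It does not defend the rule: the criterion is absent from text that sets out to state one, the status of the chosen model is open, and the plain reading gives a model that cannot be fitted.

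**Conclusion.** The point holds as a badly fixed rule that should be corrected, and does not amount to an invalid primary analysis. The H1 model depends on an undefined comparison, and which result is primary is unclear. On the plain reading (continuous T0 score, common slope, unstructured covariance) the adjusted likelihood is unbounded.

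The practical damage is to fitting and inference. Under the assumed dropout mechanisms, a compound-symmetry workaround gives an SE about 8% too small and a type I error of about 0.07. Re-entering T0 does nothing for missing at random, because T0 is already in the likelihood. Treatment type changes the estimand only if it means treatment received and enters with time; on the plan's figures the contrast then moves from 0.42–0.51 to 0.60.

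**What to change.** Delete the comparison-and-switch rule and name one adjusted primary model in advance, using T0 CATS-2 once.

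- **Preferred:** the mixed model with T0 and T1 as outcomes, unstructured covariance, baseline means constrained equal across arms, and age, gender and number of traumatic events each interacting with time. The time interactions matter, because with complete data a covariate that is constant over time and has no interaction leaves the group-by-time contrast unchanged. This keeps all randomised participants, as the plan intends.
- **Alternative:** ANCOVA of T1 on T0 with the same covariates. It drops children without a T1 score, and the text should say so.

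Remove treatment type from the intention-to-treat covariates. Report the unadjusted model as a labelled sensitivity analysis whatever it shows.

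The cost is a wording change and a few degrees of freedom: three covariates with their time interactions are six fixed effects, less the one for group at baseline.
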